### Interventions

We will use n-acetylcysteine (NAC) 900 mg in the effervescent tablet preparation as study drug. NAC is manufactured by BioAdventex Pharma Inc., Canada, based on good manufacturing practice standards. One intervention group will receive NAC at a dose of 1800 mg divided twice daily with second line MDR-TB drugs and another intervention group will receive NAC at a dose of 900 mg second line MDR-TB drugs. The control group will receive only second line MDR-TB drugs.

Participants will stop the use of trial medications if there will be any serious adverse events related to the use of NAC for instance allergic reactions or if a participant opts to withdraw from continuing with research participation.

Study nurses will be responsible for observing the participants taking the investigational medicinal product (IMP) during the treatment phase. Study nurses will provide the participants daily IMP and will document administration in the IMP treatment adherence chart. The site trial pharmacist/delegated dispenser will be responsible for dispensing the IMP. Accurate accountability records will be kept by the site to assure that the IMP will not be dispensed to any person who is not a subject under the terms and conditions set forth in this protocol, i.e., delivery to site, inventory at site, use by subject, destruction etc. The investigator/designee will immediately inform the sponsor of any quality issues arising with respect to the IMP. The sponsor will take whatever action is required should such a situation arise. The investigator undertakes to use the IMP only as indicated in this protocol.

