### Assignment of interventions

This is an open label thus research participants and the investigator team and health care providers will be aware of the assignment. The later includes clinicians, and data collectors.

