## Statistical methods

### Statistical methods for primary and secondary outcomes

The primary efficacy analysis will be conducted using laboratory measurement. Analysis that will be performed includes both Modified Intent to Treat (MITT) defined as analysis of all randomised participants and a Per Protocol (PP) defined as comparison of three arms; control with either 900 mg OD or 900BD or both intervention arms in participants who completed the treatment originally allocated.

The difference in the proportion of patients with ADRs (as defined by the primary efficacy endpoint) between each treatment arm and control arm will be calculated with 95% confidence interval using standard methods**.** In addition, hearing threshold level will be analysed over time using mixed effect models to account for the longitudinal nature of the data. Mean differences between arms in change from baseline (with 95% confidence intervals) will be derived from the fitted model.

The incidence of severe adverse drug reactions as defined by Common Terminology Criteria for Adverse Event (CTCAE) will be calculated in percentage of affected individuals in each arm during the exposure time period of 6 months and the relative risks will be estimated. Time to stable conversion in both phenotypic and molecular (TB molecular bacterial load assay) MTB monitoring methods will be calculated and compared in each arm using adjusted and unadjusted hazard ratio with log-rank test. Furthermore, the rate of patients in each arm converting to negative sputum culture at 4 or 6 or 8 months after treatment initiation will be estimated. Kaplan-Meir estimator will be used to estimate the proportion of patients converting to negative culture and MBLA by specific time.

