### Adverse event reporting and harms

Adverse events will be collected by the investigator from the time a subject sign the Informed Consent Form through to their end of follow-up visit. Participants that will be early withdrawn, will only have SAEs collected at the time of withdrawal. Any AE (serious or non-serious) observed by the investigator or reported by the subject will be recorded on the Adverse Event Case Report Form. The investigator will review each AE and assess its severity and relationship to drug treatment based on all available information at the time of the completion of the case report form. AE with relationship with drug treatment will be termed as ADRs and severity grading will be according to the CTCAE.

In the case where an overall diagnosis cannot be made, each specific sign and/or symptom will be recorded as individual AEs. Documentation of the date of onset, and stop date (duration) if applicable will be done. The AEs will also be described in severity, and action taken with IMP while concurrently describing the action taken to the participant. The outcome and relationship to IMP will be recited. Also, the occurrence and seriousness of the AEs will be documented.

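### The per-protocol set drops participants who stop NAC for an adverse drug reaction, so in the ADR comparison it can hide NAC harm or show spurious benefit, and the unaffected all-randomised analysis is not given priority

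*Protocol article*

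**What the plan says.** The section on statistical methods for primary and secondary outcomes plans two analyses together. One is a "Modified Intent to Treat (MITT) defined as analysis of all randomised participants". The other is a per-protocol comparison of the three arms "in participants who completed the treatment originally allocated". Neither is named as leading. The quantity estimated is "The difference in the proportion of patients with ADRs (as defined by the primary efficacy endpoint) between each treatment arm and control arm", with a 95% confidence interval.

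Three other places bear on who is left in the PP set:

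- Interventions, on stopping: "Participants will stop the use of trial medications if there will be any serious adverse events related to the use of NAC". The other reason given for stopping is "if a participant opts to withdraw from continuing with research participation".
- Interventions, on the comparator: "The control group will receive only second line MDR-TB drugs".
- Adverse event reporting and harms, on the outcome: "AE with relationship with drug treatment will be termed as ADRs". As worded, this covers events related to NAC as well as to the second-line drugs.

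**The concern.** Read together, these rules make the outcome decide who is analysed. A participant stopped under the NAC rule has had an ADR and has also not completed allocated treatment, so PP deletes both the participant and the event. No control can be deleted this way.

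Two features of the trial could make this matter more. First, the article says "This is an open label thus research participants and the investigator team and health care providers will be aware of the assignment", so the judgement that an event is related to NAC, which triggers stopping, is made knowing the arm. (The Concealment mechanism section also speaks of blinding, and the two statements do not agree.) Second, the Discussion cites gastrointestinal intolerance 1.4 to 2.2 times as frequent with NAC. Those events are not described as serious, so they show that NAC-related events are plausible, not how many would trigger the rule.

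Tolerability of NAC and a dose comparison are among the questions the trial is meant to inform, and its results are to guide a pragmatic trial. If the two analyses disagree, a reader has no stated basis for preferring the one that keeps every case.

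**Working it through.** **Inputs from the article.** There are 20 participants per arm, 60 in total, with a 10% allowance for withdrawal or non-evaluability (Sample size). The stated total reproduces as 60 × 1.10 = 66, or 22 per arm. There is no formal power calculation. The article gives neither an expected ADR risk in this population nor a rate of stopping NAC, so both are assumptions below.

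**Step 1: equal ADR risk in all arms, cases lost from a NAC arm only.** Let n = 22, let p be the ADR risk in every arm, and let k be the number of ADR cases removed from the NAC arm because NAC was stopped. Then

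PP risk in the NAC arm = (np − k)/(n − k), and the spurious difference is that value minus p.

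At p = 50%, for example, there are 11 cases. With k = 2 this gives 9/20 = 45.0%, a difference of −5.0 points.

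| Assumed ADR risk | k = 1 | k = 2 | k = 3 |
|---|---|---|---|
| 20% | −3.8 | −8.0 | −12.6 |
| 50% | −2.4 | −5.0 | −7.9 |
| 80% | −1.0 | −2.0 | −3.2 |

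Entries are percentage points; negative values favour NAC. The all-randomised analysis has k = 0, so its difference is 0 in every cell.

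**Step 2: NAC-related events are extra harm.** Suppose background risk is 50% in all arms and a further 10% of a NAC arm has a NAC-related serious event, independently of the background.

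- All randomised: 1 − (1 − 0.50)(1 − 0.10) = 55%, against 50% in control, so +5.0 points.
- PP: the 10% are removed and the remainder have 50%, so 0 points.

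Here PP shows no protection. It hides a real 5-point harm.

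**Step 3: control cases are also lost.** The article does not say whether a participant whose second-line drugs are stopped or changed for an ADR has completed treatment. Regimen modification due to ADRs is itself a listed secondary endpoint, so it is expected. With 11 cases among 22 in each arm:

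- 2 NAC and 2 control cases removed: 9/20 − 9/20 = 0.
- 1 NAC and 3 control cases removed: 10/21 − 8/19 = 47.6% − 42.1% = +5.5 points, against NAC.

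**Step 4: scale against precision.** The 95% half-width for a difference of two proportions at 22 per arm is 1.96 × √(2p(1 − p)/22). This is 23.6 points at p = 20% or 80%, and 29.5 points at p = 50%. Every shift above lies inside it.

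**The case against.** The strongest reply is that the analysis which avoids the problem is already planned, in the same sentence, on everyone randomised. NAC-related events are also listed separately as a safety endpoint, and severe ADRs are to be reported by arm. A distorted PP result would therefore not stand alone. This point stands, and it is the main reason the concern is moderate.

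A reader might infer that PP must produce apparent protection. The documents do not support that. It follows only if overall ADR risk is equal across arms with the stoppers included, for example because they would have had an ADR anyway. If NAC-related events are additional, PP masks harm (Step 2). If control cases are lost too, the bias can vanish or reverse (Step 3).

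A reader might also infer larger shifts by supposing that a fifth of an arm stops. The article gives no such rate. The rule is limited to serious NAC-related events, and the only attrition figure is 10% for withdrawal or non-evaluability, about two participants per arm.

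The trial is exploratory and unpowered, and its intervals will be wide. That limits what any one estimate can show, but it does not remove a known source of bias.

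Finally, PP detail is often left to an analysis plan, which is not shown here. But the article does not leave this open: it states a completion rule, and that rule conflicts with the endpoint. The modified intention-to-treat label is only terminology, since the definition given excludes nobody.

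**Conclusion.** The point holds in limited form. As written, PP selects on the outcome after randomisation, and one route out of it exists only in the NAC arms. Taken alone, that route moves the ADR comparison toward NAC, either by concealing harm or by showing benefit that is not there. The size is about 1 to 13 points for one to three removed cases in an arm of 22, at assumed equal ADR risks of 20% to 80%.

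This rests on three assumptions: that NAC-related events count as ADRs, as the harms section is worded; that the number removed is of this order; and that control cases are not lost as well. The direction of the overall PP bias is not fixed by the documents, because completion is not defined for participants whose second-line regimen changes. The all-randomised analysis is free of this exclusion but has no stated priority. Severity is moderate.

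**What to change.** Amend the statistical methods as follows:

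1. State that the all-randomised analysis leads for the ADR endpoints and that PP is supportive only.
2. In PP, do not exclude a participant who stops or changes treatment because of an ADR. Keep that participant and count the event, in every arm.
3. Handle participants who stop for other reasons by one rule applied to all arms, for example censoring at the time of stopping, with the ADR proportion then estimated by a method that allows for censoring.

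The third item is needed because simply deleting those who stop NAC without an ADR would create the opposite error. If 10% of a NAC arm were removed that way at a true risk of 50%, the PP risk would be 0.50/0.90 = 56%.

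The cost is a few sentences. Adverse events, their dates and the action taken with the study drug are already to be recorded, so no new visits or data are needed. Recruitment was in progress at publication, so the change should be documented before database lock. The downside is that PP becomes less of a pure completer analysis, and censoring assumes that stopping for other reasons is unrelated to later ADR risk.

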**Discussion:**

Given that NAC promotes synthesis of glutathione, an intracellular antioxidant that combats the impact of oxidative stress, it may protect against medication induced oxidative damage in organs such as liver, pancreas, kidney, and cells of the immune system. This randomized controlled trial will determine if NAC leads to fewer ADRs, and if this protection is dose dependent. Fewer ADRs among patients treated with MDR-TB may significantly improve treatment outcomes for multidrug regimens that necessitate prolonged treatment durations. Conduct of this trial will set the needed infrastructure for clinical trials.

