### Hypothesis II

Administration of oral NAC at a dose of 900 mg twice a day in combination with second-line during treatment of multidrug resistant tuberculosis (MDR-TB) will protect more than the dose of 900 mg daily against occurrence of serious adverse events without interfering with the effect of second line anti-TB regimen.

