## Trial design

NAC trial is a phase 2b randomized open labelled superiority trial with three parallel groups and a primary endpoint of occurrence of ADRs at any time during treatment for MDR-TB.

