### Sample size

This is a pilot trial to collect information about the effect of NAC that will potentially guide a future larger trial, thus there was no formal power calculation. Therefore, the sample size for the proposed trial will be 20-per arm and thus 60 participants will be enrolled for three arms. However, previously we have found a withdrawal/non-evaluable subject rate from our previous TB clinical trials estimated at 10% [33]. Therefore, a total of 66 MDR-TB patients will be recruited for this clinical trial [34].

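### Hypothesis II and the abstract promise a twice-daily versus once-daily answer, but the analysis names no such contrast, and the wording claims more than a pilot of 20 per arm can give

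*Protocol article*

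**What the plan says.** All places are in the protocol article.

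- **Hypothesis II:** NAC 900 mg twice a day "will protect more than the dose of 900 mg daily against occurrence of serious adverse events", without interfering with the second-line regimen. Hypothesis I makes the same non-interference claim for 900 mg daily.
- **Abstract, Discussion:** the trial "will determine if NAC leads to fewer ADRs, and if this protection is dose dependent".
- **Trial design:** a "phase 2b randomized open labelled superiority trial".
- **Primary objective:** an exploration of preliminary evidence on each NAC dose against control.
- **Sample size:** a pilot, "thus there was no formal power calculation"; "the sample size for the proposed trial will be 20-per arm and thus 60 participants will be enrolled for three arms", raised to 66 for 10% loss.
- **Statistical methods for primary and secondary outcomes:** the difference in ADR proportion "between each treatment arm and control arm will be calculated with 95% confidence interval". The per-protocol text sets control against once daily, twice daily or both. Severe ADRs are reported by arm with relative risks, no reference arm being given. Mean differences between arms come from a mixed model (hearing threshold here, ADRs in the abstract), no pairs being given. "Time to stable conversion in both phenotypic and molecular" monitoring is compared by hazard ratios with a log-rank test.
- **Secondary endpoints, Efficacy:** the culture time-to-event endpoint is time to the first negative culture.

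**The concern.** A stated hypothesis and a headline promise concern one dose against the other, while every contrast that the analysis section spells out has control on one side. Someone who follows the section literally finishes with two differences from control and no estimate, or interval, for the difference between doses. The natural temptation is then to set the two results side by side and read a pattern such as one interval excluding zero and the other not as a dose response. The key feasibility questions say the results will guide a pragmatic trial, so such a pattern could steer the choice of dose.

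The same gap between claim and design appears twice more. Superiority and determining an effect are confirmatory words for a trial that declares itself an unpowered pilot. And the hypotheses assert non-interference, for which the bacteriological analysis offers a comparison designed to detect a difference, on a culture endpoint that is defined in two ways.

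**Working it through.** **1. The plan's own figure.** 20 × 3 = 60, and 60 × 1.10 = 66, which is 22 per arm. (Dividing instead gives 60 / 0.9 = 66.7, so 67; the gap is immaterial.) The article states no power, event rate or significance level. Below, two-sided 5% is taken from the 95% intervals, n = 20 per arm from the sample-size section, and every event rate is an assumption unless its source is given.

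**2. Which pairs are named?**

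| Analysis | Pairs named | Twice vs once daily? |
|---|---|---|
| Difference in ADR proportion | each NAC arm vs control | no |
| Per protocol | control vs either or both NAC arms | no |
| Severe-ADR relative risk | none | possible, not stated |
| Mixed-model mean differences | none | possible, not stated |

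**3. What separate comparisons with control can show.** Assume 50% on control and 25% in both NAC arms, so the doses are equal. Let q(a) be the probability that a NAC arm differs significantly from control when control has a events out of 20. Both comparisons share that control arm, so

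P(twice daily alone) = Σ P(a) q(a) [1 − q(a)] = P(twice daily significant) − P(both significant).

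Exact binomial enumeration gives:
- pooled z: 0.375 − 0.208 = 0.167;
- Fisher: 0.269 − 0.127 = 0.142.

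Exactly one dose is significant in twice that share: 33% (z) or 28% (Fisher). A direct test of 25% against 25%, enumerated the same way, is falsely significant in either direction in about 5% (z) or 2% (Fisher).

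**4. Precision of the direct contrast.** Half-width of the 95% CI = 1.96 × √(2p(1−p)/20). At p = 0.25 this is 1.96 × √(0.375/20) = 0.268, or about 27 points. The contrast is feasible but imprecise, hence exploratory.

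**5. Power at 20 per arm.**

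| Rates | z, normal approximation | Fisher, exact |
|---|---|---|
| 50% to 25% (assumed) | 37% | 27% |
| 20.8% to 10.4% (bedaquiline-related ADR rate in the background; halving assumed) | 14% | 8% |
| 25% vs 12.5%, dose against dose (assumed) | 17% | 10% |
| 37.5% to 0% (liver injury in the cited trial of patients aged 60 or over with drug-susceptible TB) | 89% | 92% |

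In the last row the normal approximation is poor; exact enumeration of the pooled z test gives 97%.

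**6. Non-interference.** With an assumed 18 conversions per arm, SE(log HR) = √(1/18 + 1/18) = 0.333. An observed hazard ratio of 1.0 then has 95% CI exp(±1.96 × 0.333) = 0.52 to 1.92. A log-rank test can be entirely non-significant while conversion at little more than half the control rate remains compatible with the data.

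**7. Culture endpoint.** First negative culture and stable conversion are different events: a first negative that is followed by a positive counts for one and not for the other.

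**The case against.** - **The dose contrast is not excluded.** This stands. The relative risks and the mean differences between arms could include twice against once daily. Hypothesis II is about serious events, so the severe-ADR analysis is its nearest match, and that analysis is not limited to control. A reader might infer that the plan contains no dose comparison at all; the text supports only that none is named. A full list of pairs may well be left to an analysis plan that is not shown. But where this section does name pairs, they are the wrong ones for Hypothesis II.
- **No misreading is planned.** This also stands. A reader might infer that dose response will be judged from which comparison is significant, or non-interference from a non-significant log-rank test. The article says neither. For ADR proportions it promises intervals, not tests. The probabilities in the working measure a risk left open, not a stated rule.
- **A pilot needs no power calculation.** Agreed, and its absence is openly declared. A reader might infer that the sample is too small and should grow, or that it could never show superiority. Neither follows: the aim is exploratory, and an effect as large as 37.5% to 0% would be well powered, although it comes from an older population with drug-susceptible TB and a narrower endpoint.
- **Interference is examined in other ways.** Hazard ratios, Kaplan-Meier estimates and pharmacokinetic models are planned. The pharmacokinetic work addresses drug exposure, not bacteriological response, so caution about the log-rank test remains useful. What is new here is the interval and the rule of interpretation.

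**Conclusion.** The point holds in a limited form. The article promises an answer on twice daily against once daily and commits to no contrast that gives it. Comparisons with control cannot stand in for that contrast: under the assumed 50%, 25% and 25% at 20 per arm, equal doses would show twice daily alone as significant in roughly one trial in six or seven (17% or 14%). That figure depends on the assumed rates and on someone reading significance in that way.

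The superiority label and the promise to determine the effect conflict with the exploratory objective and the declared lack of a power calculation. This is a conflict of wording, not a fault in the sample size. Power is low for moderate effects under assumed rates and high for near-elimination of a common event.

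The two culture endpoints need reconciling; the article gives no ground for preferring one. These are inexpensive corrections that should be made before analysis.

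**What to change.** 1. **Statistical methods.** Add, as exploratory, the twice-daily minus once-daily difference in ADR proportion with its 95% CI, and the matching severe-ADR relative risk with its 95% CI. State that dose dependence will be judged from this contrast and not from separate comparisons with control.
2. **Abstract and Trial design.** Replace the promise to determine the effect and the superiority label with wording that fits an exploratory pilot, such as estimating the effect and its uncertainty.
3. **Non-interference.** Report the culture-conversion hazard ratio with its 95% CI, and state that a non-significant log-rank test will not be taken as evidence that NAC leaves the regimen's effect intact.
4. **Culture endpoint.** Use one definition in the endpoint list and in the analysis section, or list both as separate endpoints.

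Cost: a few sentences and one further contrast from data already collected. No patients, visits or tests are added. The stated claims become more modest, and the interval between doses will be wide (about ±27 points at an assumed 25% in both NAC arms), which should be said in advance.

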**Methods:**

This is a proof-of-concept randomized open label clinical trial with 3 treatment arms including a control arm, an interventional arm of NAC 900 mg daily, and an interventional arm of NAC 900 mg twice-daily administered during the intensive phase of MDR-TB treatment. Patients initiating MDR-TB treatment will be enrolled at Kibong’oto National Center of Excellence for MDR-TB in the Kilimanjaro region of Tanzania. The minimum anticipated sample size is 66; with 22 participants in each arm. ADR monitoring will be performed at baseline and daily follow-up over 24 weeks including blood and urine specimen collection for hepatic and renal function and electrolyte abnormalities, and electrocardiogram. Sputum will be collected at baseline and monthly thereafter and cultured for mycobacteria as well as assayed for other molecular targets of *Mycobacterium tuberculosis*. Adverse drug events will be analysed over time using mixed effect models. Mean differences between arms in change of the ADRs from baseline (with 95% confidence intervals) will be derived from the fitted model.

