## Key questions on feasibility

Tanzania is one of the sub-Saharan African countries facing a high burden of tuberculosis (TB) including the multidrug resistant (MDR)-TB and other infectious diseases, however the capacity to conduct research, particularly clinical trials, has been limited. We proposed to conduct a clinical trial among MDR-TB patients with the mains components of toxicity reduction and capacity development in clinical trials in Tanzania.To our knowledge, this is the first registered global trial to examine the protective effect of N-acetylcysteine (NAC) on occurrence of adverse drug reaction in MDR-TB patients treated with current recommended regimens that prioritize all-oral medications.

What uncertainties existed regarding feasibility?It was uncertain whether Tanzanian institutes would execute both sponsor/investigator responsibilities and trial management roles to address clinical research questions especially in one of the priority infectious diseases, MDR-TB.It was also uncertain whether a clinical trial unit established with managers, physicians, trialists and laboratory scientists would be set to execute all relevant clinical trials processes and confront infectious diseases using MDR-TB as a model disease.

What are the expected implications of the feasibility findings for the main study?This clinical trial aimed to minimize occurrence of adverse drug reactions in MDR-TB patients that would have a direct patient benefit but with additional components of the trial capacity for laboratory scientists, research trialists in order to create a rapid response infrastructure for other infectious diseases of public health priority. Furthermore, the trial will explore the preliminary evidence on the effect of NAC on the results that will guide design of the pragmatic clinical trial in Tanzania.

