## Introduction

### Background and rationale

The crisis of multidrug-resistant tuberculosis (MDR-TB), defined as point mutations of *Mycobacterium tuberculosis* (MTB) chromosomes resulting in strains that are resistance to isoniazid and rifampicin, key medicines for the treatment of TB, continues to worsen [1]. In 2019, the World Health Organization (WHO) estimated 484,000 cases of MDR-TB, while approximately 156,000 were enrolled to initiate treatment. This marked a 21% increase in enrolment compared to the 2016 report [2]. With the growing epidemic of MDR-TB, further exacerbated by the COVID-19 pandemic [3], and a greater proportion of people accessing treatment, there is further urgency to assure treatment regimens are tolerable and completed without interruption which poses risk to individual outcomes and *M. tuberculosis* strains with amplified drug resistance [4]. Despite the priority for tolerable regimens, medicines used to treat MDR-TB are referred to as “second-line” because of reduced potency and a worse side effect profile [5]. Regimens are constructed of 4–6 drugs based on the susceptibility profile of the infecting *M. tuberculosis* strain, drug-drug interactions or individual contraindications, and supply chain availability [6]. New and repurposed drugs have improved the efficacy and shortened the duration of MDR-TB treatment but those medications have significant and often overlapping toxicities [7]. Based on data from controlled trials and large operational studies, the WHO has recently prioritized bedaquiline, linezolid, newer generation fluoroquinolones (moxifloxacin or levofloxacin), and clofazimine for the treatment of MDR-TB as well as consideration of other new agents such as delamanid and conventional anti-TB drugs such as cycloserine, pyrazinamide, ethionamide/prothionamide, and ethambutol to complete a multi-drug regimen [8]. While medications requiring intravenous or intramuscular injection are no longer preferred, there are some uncommon clinical scenarios where TB treatment programs or patients themselves may opt to include an injectable aminoglycoside (amikacin or streptomycin) or a carbapenem with beta-lactamase inhibitor (meropenem/clavulanate or imipenem-cilastin/clavulanate).

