### Eligibility criteria

MDR-TB participants will be eligible, if they are able and willing to provide a written informed consent prior to participation, with age range between 18 and 65 years. They should be newly diagnosed with MDR-TB without a history of using or being on MDR-TB treatment. Decisions on composition of the MDR-TB treatment regimen and timing of initiation will be made by the treating clinicians, but study participants will only be eligible if Karnofsky score of ≥ 50 defined as individuals requiring less considerable or frequent medical care. Female participants should not be pregnant as confirmed by urinary pregnant test to ensure homogeneity of the participants.

Other exclusion criteria include people with previous existing pathology which will preclude testing such as severe baseline hearing loss, central nervous system pathology (i.e., major head trauma, meningitis, encephalitis, or brain metastasis), or untreated mood disorders such as schizophrenia, schizoaffective disorder or psychotic disorder, or using psychotherapeutics like imipramine, and escitalopram. Similarly, participants with known comorbid conditions such as severe liver or renal diseases will be excluded.

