### Secondary end-point is based on safety and tolerability

Patients will be daily assessed for adverse events including vital signs, physical examinations, routine clinical laboratory tests such as complete metabolic panel, complete blood count, and urinalysis, and interval assessment of electrocardiogram and for those using injectable agents, audiometry testing.Proportion of adverse eventsProportion of adverse events related to experimental treatment

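### The statistical methods assign the mixed model to hearing threshold, measured only in the uncommon injectable users, while the abstract assigns it to change in ADRs; the two sections need reconciling

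*Protocol article*

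**What the plan says.** All references are to the protocol article.

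- **Statistical methods for primary and secondary outcomes.** After a difference in the proportion with ADRs, the section adds that "hearing threshold level will be analysed over time using mixed effect models to account for the longitudinal nature of the data". It continues: "Mean differences between arms in change from baseline (with 95% confidence intervals) will be derived from the fitted model". No other outcome in the section is given a model of this kind, although the section opens by basing the primary efficacy analysis on laboratory measurement.
- **Secondary end-point (safety and tolerability).** Blood tests, urinalysis and ECG are listed for patients generally. Hearing is restricted: "for those using injectable agents, audiometry testing".
- **Background and rationale.** Injectables are described as no longer favoured, with "uncommon clinical scenarios where TB treatment programs or patients themselves may opt to include an injectable aminoglycoside".
- **Key questions on feasibility.** The trial concerns patients "treated with current recommended regimens that prioritize all-oral medications".
- **Eligibility criteria.** "Decisions on composition of the MDR-TB treatment regimen and timing of initiation will be made by the treating clinicians", so the design does not fix how many participants receive an injectable.
- **Abstract, Methods.** Here the mixed model is for adverse drug events, and the derived quantity is "Mean differences between arms in change of the ADRs from baseline".
- **Adverse event reporting and harms.** An ADR is an adverse event judged related to drug treatment.

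**The concern.** The outcome, the people measured and the model do not match. The one outcome in the statistical methods that receives a between-arm longitudinal comparison is recorded only in a subset that the document expects to be small. The Discussion says that withholding the aminoglycoside removes some of the hearing risk, while liver toxicity, cytopenias and neuropathy remain. The model is therefore attached to a toxicity expected to recede.

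The abstract does not resolve this. It uses almost the same sentence for a different outcome. That version has its own problem, because an event defined by its relation to treatment has no pre-treatment value from which to compute a change.

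At stake is what a pilot of 66 can pass on to the larger trial it is meant to guide. Repeated liver, kidney, marrow and QTc values have a baseline and are collected without the injectable restriction. As the statistical methods are written, they inform the comparison only through yes/no ADR counts.

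**Working it through.** **1. Sample size (Sample size section).** 20 per arm gives 3 × 20 = 60, plus a 10% allowance: 60 × 1.10 = 66, the stated figure. Dividing instead, 60 / 0.90 = 66.7, rounds up to 67, a trivial difference. I use 20 evaluable per arm. No power calculation is given, so there is none to reproduce.

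**2. Participants with hearing data.** The document gives no injectable share *p*, so *p* is an assumption. The expected number per arm is 20 × *p*. The chance that every arm has at least 2 contributors is [P(X ≥ 2)]³ with X ~ Binomial(20, *p*).

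| Assumed *p* | Per arm | Total | All three arms ≥ 2 |
|---|---|---|---|
| 2% | 0.4 | 1.2 | 0.000 |
| 5% | 1 | 3 | 0.018 |
| 10% | 2 | 6 | 0.225 |
| 20% | 4 | 12 | 0.806 |
| 30% | 6 | 18 | 0.977 |

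Using 22 per arm changes little: at 10%, 2.2 per arm and a probability of 0.289.

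**3. Precision.** Take one change score per participant, *m* participants per arm, and an SD pooled over three arms. The 95% CI half-width for a difference between two arms, in SD units, is t(0.975; 3*m* − 3) × √(2/*m*).

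- *m* = 2 (3 df): 3.18
- *m* = 4 (9 df): 1.60
- *m* = 20 (57 df): 0.63

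With *m* = 1 there are no residual degrees of freedom.

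**4. Gain from adjusting for baseline.** With equal variances and baseline-to-follow-up correlation ρ, a change score has variance proportional to 2(1 − ρ) and a baseline-adjusted comparison to 1 − ρ². The ratio is (1 + ρ)/2. At assumed ρ = 0.5 it is 0.75, a 25% reduction; at ρ = 0.7 it is 0.85, a 15% reduction. The change score is the right comparator because it is what the plan specifies.

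**5. Abstract against statistical methods.** Both derive between-arm mean differences in change from baseline, with 95% confidence intervals, from a mixed model. One names hearing threshold, the other ADRs. Eligibility requires no previous MDR-TB treatment, so an ADR to the MDR-TB regimen cannot be present before that regimen starts.

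**The case against.** Several stronger readings are tempting, and the document does not support them.

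- *The hearing model cannot be fitted.* Not shown. The injectable share is not given, the description of injectables as uncommon concerns MDR-TB practice in general, and clinicians choose the regimen. Audiologists are named among the outcome assessors, so some testing is expected. At 20% to 30% a model could usually be fitted, though imprecisely. Fig. 1 (the schedule of events) is not shown, so wider audiometry cannot be excluded.
- *The laboratory data get no model or go unused.* They feed the ADR proportions, which match the stated objective of clinical or laboratory-based ADRs. The abstract names a mixed model for adverse drug events, and population PK models are planned for plasma concentrations.
- *Unblinded clinicians select the hearing subset.* The order of regimen choice and allocation is not stated. If the regimen is chosen first, injectable use is simply a baseline subgroup.
- *Hearing is outside the endpoints altogether.* Audiometry is listed among the assessments under the secondary safety end-point.

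It is also fair to say that hearing is introduced as a supplement, that models for individual laboratory measures are commonly left to a SAP, and that laboratory values behind an ADR do have baselines, so the abstract may be loose wording.

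What remains is not an omission. The statistical methods positively choose an outcome and a model, the abstract chooses another, and the first choice conflicts with the document's own account of who is measured.

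**Conclusion.** The point holds as a mismatch and a contradiction. The statistical methods tie their only outcome mixed model to a measurement made in injectable users, and the abstract ties the same analysis to a quantity without a workable baseline.

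The size depends on the assumed injectable share. At 5% to 10% the hearing comparison would be too thin to inform: the chance that every arm has even 2 contributors is 2% to 23%. At 20% it could probably be estimated, but with an interval about 2.5 times as wide (1.60 / 0.63) as for a measure taken on everyone. These figures assume 20 evaluable per arm and one change score each; repeated visits would alter the half-widths.

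The ADR proportions are unaffected. The matter should be corrected because it determines which between-arm estimates the pilot will deliver.

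**What to change.** Reconcile the abstract's Methods with the statistical methods section:

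- Apply the mixed model to a short prespecified list of continuous measures collected on all randomised participants, for example log ALT and AST, bilirubin, creatinine, haemoglobin or platelets, and QTc.
- Include visit, arm and arm-by-visit terms, with the baseline value as a covariate. Report arm differences with 95% confidence intervals, labelled exploratory.
- Keep ADR occurrence as a proportion or time-to-event outcome, and drop the change-from-baseline wording for ADRs in the abstract.
- Summarise audiometry descriptively in those tested. If it is in fact done in everyone, correct the safety end-point section instead.

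The cost is analysis wording, provided the schedule of events confirms repeated measurement of each listed variable. The downside is several exploratory outcomes without multiplicity control, which is why the list should be short.
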